### Randomization

Included participant will be randomly divided into the ARQE group and the CBTI group according to a 1:1 ratio. Block randomization is used with 4 block size to generate two different sets of random numbers lists. Random number tables are generated by researchers who have no contact with participants or evaluators. Each random number is sealed in a pre-prepared opaque envelope with the patient’s serial number on it. After the participant has been certified and signed a written informed consent, participant will open an envelope with patient serial number is opened and know the group of participant belongs to. Informed consent is available by email to corresponding authors. Because of the significant difference between massage treatment and CBTI, double-blinded method cannot be used. Thus, it is important to ensure the data analyst does not know the grouping and intervention method of the insomnia patients.

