### Participants

#### Recruitment strategy

Participants will be recruited through advertisement and referrals starting in July 1, 2020. There are three main strategies for recruiting insomniacs. The first strategy was to recruit participants from the outpatient and inpatient departments of Yueyang Hospital of Integrated Traditional Chinese and Western Medicine affiliated to Shanghai University of Traditional Chinese Medicine. Second, printed recruitment posters will be distributed at the Shanghai university of traditional Chinese medicine and in nearby communities to recruit potential research subjects. Third, we will advertise our research through the Internet and social media (e.g., WeChat) to attract patients who may be willing to participate.

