The results of this trial are expected to evaluate the efficacy of ARQE in the treatment of patients with insomnia through the degree of changes in brain activation and the related results of the clinical scale in order to confirm whether ARQE can effectively alleviate insomnia. We believe that the results of this study will provide a new solution for the treatment of insomnia for other researchers to learn from. This trial also has certain limitations. Due to the significant difference between “ARQE” and “CBTI,” blinding methods cannot be used for therapists and subjects, leading to a certain risk of bias in this experiment. Therefore, we set the same intensive training frequency to ensure the same frequency of contacting between the two groups of subjects and therapists, establish the same good doctor-patient relationship, and reduce the resulting differences. In order to ensure the authenticity of the experimental data and reduce the deviation due to the experimental process, we will strictly randomize the subjects and make the therapists, evaluators, and statisticians cannot contact each other. The neuroimaging research in this trial is only at the exploratory stage, and the sample size is limited. In future studies, the sample size can be increased to obtain more convincing evidence.

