## Trial status

This protocol is version 1. Due to the time required for recruitment and preparation, the trial began in July 2020.The trial is currently in the early stages of recruiting participants. We expect the recruitment to be completed by July 2021.

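### One fixed block size of 4, published during recruitment to an open-treatment trial, would let an informed recruiter deduce up to one third of allocations

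*Protocol article*

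**What the plan says.** The Randomization section of the protocol article sets the ratio, "Included participant will be randomly divided into the ARQE group and the CBTI group according to a 1:1 ratio", and one block size: "Block randomization is used with 4 block size to generate two different sets of random numbers lists". It does not explain what the two sets of lists are for.

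The lists come from researchers who have no contact with participants or evaluators. Each number is sealed in an opaque envelope marked with the patient's serial number, and the envelope is opened only after eligibility and signed consent. At that point the "participant will open an envelope with patient serial number is opened and know the group of participant belongs to".

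Treatment is open. The same section says "Because of the significant difference between massage treatment and CBTI, double-blinded method cannot be used", and the Discussion says "blinding methods cannot be used for therapists and subjects". (The Study design section describes participants as blinded. That conflicts with both statements and needs its own correction; I follow the two sections that give the reason.)

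The Recruitment strategy section says the trial will "recruit participants from the outpatient and inpatient departments of Yueyang Hospital of Integrated Traditional Chinese and Western Medicine", with posters and internet advertising as further routes. No other hospital is named. Trial status reports: "The trial is currently in the early stages of recruiting participants".

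**The concern.** Concealment means that whoever decides on a person's entry cannot foresee that person's arm. Sealed envelopes hide their own contents, but in a 1:1 block of 4 the earlier openings give information about the later ones. Once two of one arm have appeared, the rest of that block is known.

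The conditions that make this usable are present or plausible here. Arms become known at opening and stay visible: one group trains with a TCM doctor, while the other attends group therapy and joins a WeChat group. One hospital means that one team could follow the order of entries. The article gives the block size at a time when most allocations still lay ahead.

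There is also room for preference to act. The Background says that the group often uses ARQE in its own clinic and regards its benefit as well known. One exclusion criterion concerns communication problems and ability to perform abdominal rubbing, so it calls for judgement and bears mainly on one arm. If someone foresaw the next arm, entry could be encouraged, delayed or refused accordingly. The arms could then differ in expectation or motivation before treatment starts. The primary outcome, PSQI, rests on the answers of unblinded participants, and the planned difference is only 1.47 points.

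**Working it through.** The protocol gives no predictability figure, so there is none to reproduce.

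**Inputs.** Block size 4 and ratio 1:1 (Randomization); 114 participants (Sample size calculation). Assumption: the observer knows the block size, the list in use and every earlier allocation in it.

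**Certain allocations.** A block with two of each arm has 4!/(2!·2!) = 6 equally likely orders. An allocation is certain once one arm's two places are used.

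| Position in block | Probability that it is certain | Probability that the best guess is right |
|---|---|---|
| 1 | 0 | 1/2 |
| 2 | 0 | 2/3 |
| 3 | 1/3 (first two match) | 1/3·1 + 2/3·1/2 = 2/3 |
| 4 | 1 | 1 |
| Sum per block | 4/3 | 17/6 |

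Dividing by 4, the certain share is (4/3)/4 = 1/3, and best-guess accuracy is (17/6)/4 = 17/24 = 70.8%. Simple randomization gives 0 and 50%.

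**Applied to 114 participants.** 114 = 28 × 4 + 2, and the two left over are never certain. The expected number of certain allocations is 28 × 4/3 = 37.3, or 37.3/114 = 32.7%. Two lists of 57 (14 full blocks plus 1 each) give 2 × 14 × 4/3 = 37.3 again, provided the observer knows which list applies.

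**Effect of varying the block size.** Sequences of 114 were simulated (2,000 runs each for fixed 4 and for 4 and 6; 1,000 runs for 4, 6 and 8). The observer knew the set of sizes and all past allocations, but not the size of the current block.

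| Block sizes | Certain | Best guess right |
|---|---|---|
| 4 only | 32.8% | 70.6% |
| 4 and 6, at random | 5.5% | 69.2% |
| 4, 6 and 8, at random | 2.1% | 67.9% |

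The first row agrees with the exact result. Varying the size removes nearly all certainty but little of the guessing advantage, because an observer who sees the running imbalance can still bet on the arm that is behind. Only withholding past allocations removes that advantage.

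**The case against.** The strongest reply is that the figure describes an ideally informed observer. The article does not say that recruiting staff see or record the sequence of openings. Treatment is given by different people in the two arms, the Discussion keeps therapists, evaluators and statisticians apart, and what recruiters are told may be set out in a fuller protocol. List generation is independent, the envelopes are opaque and sealed, and opening follows eligibility and consent. These are real safeguards.

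Much of this stands, and it makes the point conditional. One third is an upper figure. If the two lists are interleaved and the recruiter cannot tell which applies, fewer allocations are certain. The point does not fall, though. None of the safeguards stops deduction from earlier openings, the separation of roles does not name those who recruit, and the article both fixed the size and disclosed it.

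Three stronger readings are tempting and are not supported:

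- A reader might infer that concealment has failed. The article contains no evidence of that.
- A reader might infer that any resulting bias is beyond repair in the analysis. Baseline PSQI and other characteristics are recorded and compared, so steering on measured factors could be seen and partly adjusted for. Unmeasured factors could not.
- A reader might take 57 per arm as a promise that blocks of 4 cannot keep, since 114 is not a multiple of 4. The Sample size section states it as an aim, and a 58/56 split raises the variance of the difference by a factor of only (57 × 57)/(58 × 56) = 3249/3248.

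**Conclusion.** The concern holds as an avoidable risk to concealment. With a fixed block of 4, up to one third of allocations (about 37 of 114) could be known in advance and about 71% guessed correctly. This rests on four assumptions: the observer knows the block size, can tell which list is in use and knows the earlier allocations; and recruitment runs through one hospital, which is inferred from the only site named. The first is easily met because the size is in print. The article does not settle the second and third. The size of any bias in PSQI cannot be derived from the document. The risk is worth reducing because the remedy is cheap and most of the sample was still to be allocated when the article was written.

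**What to change.** For envelopes not yet used:

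1. Have the independent list-maker regenerate the sequence with randomly varying block sizes, for example 4, 6 and 8. Do not disclose the sizes to recruiting, treating or assessing staff. The published size of 4 cannot be withdrawn, so the new scheme should not appear in circulated documents.
2. Keep those who screen and enrol unaware of the running record of past allocations, for instance by having someone outside screening handle the opening and hold the log.
3. State what the two sets of random number lists are for.

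The cost is a new list, new envelopes and a notification to the ethics committee and registry, a route the article already provides for protocol changes. The downside is a possible final imbalance of a few participants. With one list, an unfinished block of 8 can leave a difference of at most 4, and switching in mid-block adds at most 2. Even 60/54 raises the variance of the group difference by a factor of only (57 × 57)/(60 × 54) = 3249/3240, about 0.3%.

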### Intervention

#### ARQE group

In this study, patients with insomnia received ARQE treatment 7 times a week for 8 weeks. A TCM doctor with more than 5 years of experience will intensively practice the patient once every Sunday. Each training lasts for 50 min, including breathing techniques and mild warm-up (10 min), abdomen-rubbing qigong exercise (30 min), and finally relax (10 min). Patients will be advised to exercise ARQE independently for 50 min before going to bed from Monday to Saturday.

In order to ensure the correct posture and movement speed, before the start of the experiment, the patient will receive 3 days of training provided by a TCM doctor with more than 5 years of experience to ensure the standard movements, strength, and speed of abdomen rubbing. The specific practice method of ARQE is shown in Fig. 2.

**Fig. 2 Fig2:**
[figure not shown]
The abdomen-rubbing qigong exercise posture

#### CBTI group

In this study, patients with insomnia will receive cognitive behavioral therapy for insomnia, including 8 weeks of cognitive behavioral therapy for insomnia with an experienced psychotherapist. The psychotherapist will provide weekly group cognitive behavioral therapy on Sundays. Patients were advised to conduct 50 min of self-behavioral cognitive learning every day from Monday to Saturday to ensure the same duration of intervention in the ARQE group. At the beginning of the experiment, we added the patient to the WeChat group organized by the psychotherapist and uploaded the lecture notes of the CBTI course to the WeChat group for the subjects to review. In addition, the therapist will regularly upload learning materials related to insomnia for the subjects to learn and regularly answer patients’ questions. Considering that Chinese people are generally unwilling to express their feelings in public, the psychotherapist will actively communicate with patients through social media (WeChat) once a week.

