#### Sample size calculation

The required sample size is calculated using an estimation formula based on the difference between two sample means and standard deviations (Pittsburgh Sleep Quality Index, which is assessed using composite points of sleep quality). A previous clinical study suggests that the mean and standard deviations of Pittsburgh Sleep Quality Index (PSQI) in ARQE group(*n* = 40) after treatment are 8.45 and 2.06, while the mean and standard deviations of PSQI in CBTI group (*n* = 40) after treatment are 9.92 and 2.65 [26, 27]. The sample size is calculated in the following formula, with the two-sided significance level (α) set at 0.05 and statistical power at 0.80 [28]. Thus, a minimum sample size of 51 participants per group (102 participants in total) is calculated to provide sufficient statistical power to detect a between-group mean difference of 1.47 in treatment efficiency, defined as the change in PSQI score.

Considering a 10% loss to follow-up, we aim to recruit 57 patients in each group, in a total of 114 patients. According to fMRI studies, 15 to 30 patients are adequate to test hypotheses.

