### Statistical analysis

#### Primary outcome analysis

With previous set single blind rule, an independent statistician will analyze the clinical data by SPSS V.24.0 statistical software. Data analysis will be based on the intention-to-treat (ITT) principles. The results of ITT analysis will be compared for consistency. A *p* value < 0.05 will be considered statistically significant. Participants who fail to complete the study will be treated as having no change from baseline at all times in both groups. The Kolmogorov–Smirnov test will be used to test the normality. Appropriate transformations will be applied for non-normal distribution, The continuous variables with normal distribution will be described as mean and standard deviation, while continuous variables with non-normal distribution will be expressed by using median and interquartile interval (IQR), the categorical variable will be expressed in number and proportion.

To compare the baseline characteristics between two groups, Student’s *t* test or Mann–Whitney test will be used for continuous variables. Pearson’s *χ*-squared or Fisher’s exact will be used for categorical variables. To compare the primary and secondary outcomes between groups, continuous data will be tested by Student’s *t* test or non-parametric test. Pearson’s *χ*-squared or Fisher’s exact test will be applied for categorical data at baseline and after intervention. Repeated-measures ANOVA using the group-by-time interaction terms will be used to analyze the between-group differences. Multivariate analysis of variance will be used and the two-two comparisons among the changes in questionnaire scores with repeated measurement times for each group will be done by Bonferroni correction.

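### CBTI is given in therapy groups, but the sample size and between-group tests treat all participants as independent; if outcomes correlate within groups, the standard error is too small.

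*Protocol article*

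**What the plan says.** Under CBTI group, the protocol article describes an 8-week course led by a psychotherapist: "The psychotherapist will provide weekly group cognitive behavioral therapy on Sundays". There is further shared contact, since at the start "we added the patient to the WeChat group organized by the psychotherapist", where lecture notes are posted. From Monday to Saturday participants study on their own, and the therapist contacts them weekly through WeChat. The number and size of the therapy groups are not given, and only one psychotherapist is described.

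Under ARQE group, a TCM doctor trains the patient every Sunday. The text does not say whether those sessions are individual or shared.

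Under Randomization, individual participants are allocated 1:1.

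The sample size uses a formula for two means, "with the two-sided significance level (α) set at 0.05 and statistical power at 0.80". PSQI mean and SD for ARQE "after treatment are 8.45 and 2.06"; for CBTI they "after treatment are 9.92 and 2.65". On that basis "a minimum sample size of 51 participants per group (102 participants in total) is calculated", and 57 per group are to be recruited to allow for 10% loss. No design effect is mentioned.

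Under Primary outcome analysis: "To compare the primary and secondary outcomes between groups, continuous data will be tested by" Student's t test or a non-parametric test. A repeated-measures ANOVA with a group-by-time interaction is also named. There the only correlation addressed is that between visits of one person; no term for therapy group or therapist appears.

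**The concern.** People treated together share a therapist, session content and group dynamics, so their outcomes may be more alike than those of people treated separately. Randomising individuals does not prevent this, because the grouping arises after allocation. As described, the design is partially nested: grouped in the CBTI arm and, unless the Sunday ARQE sessions are shared, individual in the ARQE arm.

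A t test or ANOVA that ignores a positive within-group correlation counts the CBTI arm as holding more information than it does. The confidence interval is then too narrow and a false-positive result on PSQI is more likely than 1 in 20. The Discussion section's matching of contact frequency between arms does not remove correlation within a therapy group.

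**Working it through.** **Inputs from the article (Sample size calculation):** α = 0.05 two-sided, power 0.80, difference 9.92 − 8.45 = 1.47, SDs 2.06 (ARQE) and 2.65 (CBTI), 51 per arm.

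**Assumptions, not in the article:** CBTI group size m = 8; ICC from 0.01 to 0.10; clustering in the CBTI arm only.

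**1. Reproduce the stated figure.** n per arm = (SD_A² + SD_C²)(1.96 + 0.842)²/1.47², with (1.96 + 0.842)² ≈ 7.849.
- SD 2.65 in both arms: 2 × 7.0225 × 7.849/2.1609 = 51.01, which matches 51.
- SDs 2.06 and 2.65: (4.2436 + 7.0225) × 7.849/2.1609 = 40.9, or 41.
- Loss: 51/0.90 = 56.7, or 57.

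The stated 51 is therefore the full-independence figure, with the larger SD in both arms and no design effect.

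**2. Standard error and type I error.** Design effect in the CBTI arm: DE = 1 + (m − 1) × ICC. With equal SDs, true SE/planned SE = √((1 + DE)/2). Type I error = 2 × [1 − Φ(1.96/ratio)].

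| ICC (m = 8) | DE | SE ratio | Type I error |
|---|---|---|---|
| 0 | 1.00 | 1.000 | 5.0% |
| 0.01 | 1.07 | 1.017 | 5.4% |
| 0.05 | 1.35 | 1.084 | 7.1% |
| 0.10 | 1.70 | 1.162 | 9.2% |

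Simulating the unadjusted t test (40,000 runs) gave 7.1% at ICC 0.05 and 9.1% at ICC 0.10. Group size matters too. With m = 6 and ICC 0.01 the ratio is √((1 + 1.05)/2) = 1.012 and the error 5.3%. With m = 12 and ICC 0.10 the ratio is √((1 + 2.10)/2) = 1.245 and the error about 11.5%.

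**3. Power of a test that uses the correct SE, 51 per arm.** SE = √((SD_A² + SD_C² × DE)/51); power = Φ(1.47/SE − 1.96).
- SD 2.65 in both arms, ICC 0.05: SE = √(7.0225 × 2.35/51) = 0.569; 1.47/0.569 − 1.96 = 0.62; power about 73%. At ICC 0.01 and 0.10 it is 79% and 67%.
- SDs 2.06 and 2.65, ICC 0.05: SE = √((4.2436 + 9.4804)/51) = 0.519; 1.47/0.519 − 1.96 = 0.87; power about 81%, against 88% under independence. The type I error of the unadjusted test in this case is about 7.6%.

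**4. Interval width with few groups.** 51/8 is about 6.4 groups, so the CBTI variance has about 5.4 degrees of freedom. The Satterthwaite approximation with equal SDs and ICC 0.05 gives (1 + 1.35)²/(1²/50 + 1.35²/5.4) ≈ 15.4 degrees of freedom and a critical value of 2.127, against 1.984 on 100. The interval is 1.084 × 2.127/1.984 ≈ 1.16 times the planned width. The power figures in step 3 use the normal critical value and are slightly optimistic for the same reason.

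**The case against.** **The size is unknown.** The article supports no particular ICC. Shared exposure is one session a week plus a WeChat group, with individual study on the other days. At ICC 0.01 the type I error is 5.4%, which hardly matters. This stands: a reader might infer that the standard error is certainly too small, but the documents support that only conditionally on a positive ICC.

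**Power may be adequate.** A reader might infer that the trial is underpowered. The article's own two SDs still give about 81% in the middle case. The plan also keeps non-completers in the analysis as unchanged from baseline, so up to 57 per arm are analysed. Even with SD 2.65 in both arms, SE = √(7.0225 × 2.35/57) = 0.538 and power is about 78%, before any dilution from that imputation. This stands too, but spare power does not correct the type I error.

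**A random group effect may not be estimable.** The article describes one psychotherapist and one WeChat group. If the arm is in effect a single group, its effect cannot be separated from the treatment effect by any model. Recruitment runs from July 2020 to July 2021 and the course lasts 8 weeks, so successive groups, or sessions with changing membership, are plausible; neither is stated. The fix must allow for each case.

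**The ARQE sessions may also be shared.** Then clustering would affect both arms and the figures above would not apply as they stand.

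**This could be left to the analysis plan.** Group counts might be. But the article itself fixes group delivery, an independence-based sample size and the between-group tests, so the mismatch is already in the text.

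**Conclusion.** The point holds in conditional form. The article specifies group delivery of CBTI, together with a sample size and between-group tests that assume independence. For any positive within-group correlation the planned standard error is too small. Under groups of 8 and clustering in the CBTI arm only, the type I error is 5.4% to 9.2% for ICC 0.01 to 0.10, and 7.1% at 0.05. Power at ICC 0.05 with 51 per arm is about 73% or 81%, depending on the SDs used. The documents do not establish that the ICC is positive, that the trial is underpowered, or that there are several groups.

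**What to change.** State the number and size of the CBTI groups and the number of therapists, and whether the Sunday ARQE sessions are shared. Record the therapy-group ID and therapist of each CBTI participant, and of any shared ARQE session, during treatment, since membership is hard to reconstruct later. If membership changes over the course, record attendance by session, because one fixed ID would not describe the correlation.

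- **If there are several CBTI groups:** analyse PSQI with a partially nested mixed model: a random therapy-group intercept in the CBTI arm, ARQE participants as singletons unless their sessions are shared, arm-specific residual variances and small-sample degrees of freedom.
- **If the CBTI arm is in effect one group or has one therapist:** state that the group or therapist effect is confounded with arm, and limit the conclusion to CBTI as delivered by that group or therapist.

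The cost is one or two extra variables on the case report form, one random term and a wider interval. With few groups the widening exceeds the 8% from the SE ratio alone; it is about 16% in the middle case. Restoring 80% power there with SD 2.65 in both arms would take 7.0225 × 2.35 × 7.849/2.1609 = 59.9, or 60 per arm (60/0.90 = 66.7, or 67 with loss), before any small-sample allowance. With the article's own SDs, 51 per arm already gives about 81% on the same basis. The article describes recruitment as in its early stages, so recording the group can still be introduced.
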